## Introduction

Population aging is a global phenomenon that has grown rapidly and progressively all over the world because of factors such as increased life expectancy and declining birth rates. Brazil has followed this trend with a speed slightly higher than the world growth pattern (1), which has called attention both in scientific research and in the perspective of necessary public policies that promote health and quality of life to attend this demand.

The concept of quality of life is complex to be defined, and it can be interpreted in a multidisciplinary way due to the different cultural, ethical, religious, and people values that influence the way it is perceived (2). The definition of quality of life, according to the World Health Organization Quality of Life Group, is related to “individuals' perception of their position in life in the context of the culture and value systems in which they live and in relation to their goals, expectations, standards, and concerns” (3). From this conceptualization, we can understand that the perception of quality of life has its subjective, multidimensional, and contextual character for each individual.

There is no clear consensus regarding the definition of quality of life in the elderly (4). However, García and Navarro say that quality of life for the older people is a multidimensional concept that is related to their life satisfaction, autonomy, and independence in their execution of their activities of daily living (ADLs) (4). In terms of health assessment, tasks that involve their functional capacity, autonomy, and independence are known as ADLs, and it refers to basic activities related to self-care such as feeding, bathing, and dressing, as also instrumental activities lead an independent life within the community like going shopping (5). Studies show that the better the ADLs, the better the quality of life (6–9).

A longitudinal study published (10) demonstrated that older people who meditated more frequently over 59 weeks between the initiation of an 8-week mindfulness-based intervention (MBI) program and the 1-year follow-up had a greater performance in their ADL than the group that meditated less frequently.

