Randomization will be implemented using the Microsoft Excel. Each participant will be randomized individually for each of the two groups. The couples will be stratified into the same groups as it was also considered that, if they were allocated to be separated, one could teach another what was taught and then contaminate the sample. All randomization procedures will be made by a statistical professional who will only receive the identification number of the participants and will not interact with them at any time before, during, or after the intervention.

After the randomization, the participants will be invited to attend the CSR for a lecture, which we will inform which group they were randomized to and when the intervention will start. At this moment, we will hand the participants the informed consent in written form to be signed by the interested and the measure scales that were not filled during the screening such as Mindful Attention Awareness Scale (MAAS) (65, 66), Self-Compassion Scale (SCS) (67, 68), Depression Anxiety and Stress Scale (DASS-21) (69, 70), Pittsburg Sleep Quality Index (PSQI) (71, 72), and Duke Religious Index (Durel) (73, 74).

Due to the nature of the intervention, this will be a single-blind study, in which the outcomes assessment and analyses will be blind, but the participants will be aware of their group assignment.

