### Assessment and Outcomes

The first two assessment points (baseline, post-intervention) will occur over a week before the intervention and on the last meeting of the maintenance group, and the follow-up will occur 1 year after the last meeting of the intervention. For the baseline, the sociodemographic questionnaire, WHOQOL-BREF, WHOQOL-OLD, MoCA, and ADL questionnaire occurred during the recruitment; all the other scales will be applied a week before the intervention starts. The measures of the intervention group will be on sheets of paper as most of the participants are not familiar with using electronic devices. The typing of the data will be made by two people to supervise and to guarantee no typing mistake of the collected data. SurveyMonkey software will be used for data collection for control group as the participants will learn how to use it on the cognitive stimulation classes. All the instruments have been validated into Portuguese with reliable psychometric properties and are available in Supplementary Files (48, 49, 60, 61, 63, 65, 68, 70, 71, 73).

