### Primary Outcomes Measure

#### WHOQOL-BREF

Developed by the World Health Organization, the instrument is a short version of WHOQOL-100, and it comprises 26 items in which two are general about quality of life and general health, and the other 24 grouped into four domains: physical health, psychological health, social relationships, and environment. It presents Likert scale answer (1–5 points). The Brazilian validation of WHOQOL-BREF Cronbach coefficient values has satisfactory internal consistency ranging from 0.69 to 0.84 between the domains (61).

The WHOQOL-OLD module will be used as a complement to the WHOQOL-BREF to evaluate the quality of life of the elderly. The WHOQOL-OLD follows the same methodology as WHOQOL-100, but the objective is evaluating the specific quality of life of the elderly population. The module comprises 24 items evaluated by the Likert scale (1–5 points) assigned six facets such as sensory abilities, autonomy, past–present–future activities, social participation, death and dying, and intimacy. The Brazilian validation of WHOQOL-OLD also has a satisfactory internal consistency with its Cronbach coefficient between 0.71 and 0.88 (60).

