#### MoCA

This neuropsychological test assesses the cognitive function. It is a 12-item test that measures eight cognitive domains: short-term memory (delayed drawing), visuospatial abilities (cube drawing, clock drawing), executive function (trail-making test, phonemic verbal fluency, verbal abstraction), attention, concentration, working memory, language, and orientation to time. The test total score is 30 points where a score ≤26 indicates normality, and less indicates mild cognitive impairment (63, 64).

At the post-intervention, the feasibility and adherence of MBHP program among the participants will be assessed through a questionnaire created by our research group in order to evaluate the type, frequency, and length of personal meditative practice at home during the week out of the meetings, addressing potential unwanted effects as well. The frequency of the attendance to the weekly meeting will also be monitored. The dropout cases will be monitored, and we will make phone calls to them to ask the reasons why they were absent or did not go on attending the meetings. For more information about the target of each scale assessment and its time points, see Table 2 and Figure 2 to see each step of the study.

**Table 2 T2:** Overview of measures and time points (according to 2013 SPIRIT figure guidelines).

**Measure**	**Target**	**T0**	**T1**	**T2**
		**Baseline**	**Post-intervention**	**Follow up**
WHOQOL-BREF	Quality of life	X	X	X
WHOQOL-OLD	Quality of life of elderly	X	X	X
MoCA	Cognitive function	X	X	X
CDR	Dementia	X		
ADL	Activities of daily living	X	X	X
MAAS	Mindfulness trait	X	X	X
SCS	Self-compassion	X	X	X
PSQI	Sleep quality	X	X	X
DUREL	Religiosity	X	X	X
DASS-21	Psychological health	X	X	X

*ADL, Activities of Daily Living Scale; CDR, Clinical Dementia Ratings; DASS-21, Depression Anxiety Stress Asessment-21; DUREL, Duke Religious Index; MAAS, Mindful Attention Awareness Assessment; MoCA, Montreal Cognitive Assessment; PSQI, Pittsburgh Sleep Quality Index; SCS, Self-Compassion Scale; WHOQOL-BREF, World Health Organization Quality of Life–BREF; WHOQOL-OLD, World Health Organization Quality of Life–OLD*.

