### Statistical Analysis

All analyses will be conducted using intention-to-treat and per-protocol analyses following the CONSORT recommendations for reporting the results (44).

Categorical variables will be described by absolute and relative frequencies. Numerical variables will be checked for their distributions through histograms and boxplots. If considered as having normal distribution, they will be described by mean and standard deviation. Otherwise, they will be described by medians and quartiles.

The primary outcome of this study is the quality of life measured by the WHOQOL-BREF and WHOQOL-OLD, and the secondary outcomes are cognitive function measured by the MoCA, level of consciousness at present measured by the MAAS, self-compassion measured by the SCS, Psychological Health measure by DASS-21, sleep quality measured by PSQI, and religiosity assessed by the Duke University Religion Index. Sociodemographic questions (sex, age, schooling), treatment group, and time will be the independent variables.

To verify the homogeneity between the study groups regarding sociodemographic measures at the initial time of the study, the groups will be compared by means of hypothesis tests of the type: χ^2^ and/or Fisher exact for categorical variables and multivariate analysis of variance (MANOVA) and/or Kruskal–Wallis for numerical or ordinal variables. A descriptive analysis of the sociodemographic categories regarding the sex, age, and schooling of both groups will be carried out.

Measures of preintervention (T0), post-intervention (T1), and follow-up (T2) outcomes may be compared by means of MANOVA for repeated measures. If necessary, Student *t*-tests will be conducted for paired or Wilcoxon data by applying corrections by the Holm or Bonferroni method. A Pearson correlation coefficient analysis will also be performed between the means of the primary outcomes and those of the secondary outcomes to examine the degree of changes in the outcome measures over time.

The difference between the measures T0 to T1, T1 to T2, and T0 to T2 can be compared between the intervention groups in MANOVA of repeated measures by means of Mann-Whitney tests. If necessary, these models will also be adjusted to assess the effects of time and intervention group, controlling for possible moderating variables.

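### Outcome assessment is called blind, but at T1 and T2 the primary quality-of-life scales are rated by participants who know their arm

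*Protocol article*

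**What the plan says.** - **Blinding.** Recruitment, Procedures, and Randomization describes a "single-blind study, in which the outcomes assessment and analyses will be blind, but the participants will be aware of their group assignment". The same section says that participants are told their group at a lecture after randomization, before the intervention starts.
- **Primary outcome.** Statistical Analysis states: "The primary outcome of this study is the quality of life measured by the WHOQOL-BREF and WHOQOL-OLD". Under Primary Outcomes Measure both instruments are described as questionnaires with answers from 1 to 5. The Introduction defines the construct as "individuals' perception of their position in life in the context of the culture and value systems in which they live".
- **Collection.** Assessment and Outcomes states: "The measures of the intervention group will be on sheets of paper as most of the participants are not familiar with using electronic devices". The control arm uses SurveyMonkey, because its participants learn the tool in class.
- **Timing.** The same section sets the post-intervention assessment "on the last meeting of the maintenance group" and the follow-up one year after the last meeting. WHOQOL-BREF, WHOQOL-OLD, MoCA and ADL at baseline were taken during recruitment.
- **MoCA.** It is a secondary outcome, introduced with the words "This neuropsychological test assesses the cognitive function". Table 2 schedules it at T0, T1 and T2.

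**The concern.** A blind assessor protects an outcome only when the assessor makes the rating. When the participant makes it, the participant is the assessor for this purpose, and here the participant knows the arm. An assistant who merely hands over the form or reads the items aloud does not change that.

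The consequence falls on the main claim. The Introduction hypothesises that MBHP is superior to cognitive stimulation on quality of life. Baseline WHOQOL was recorded before allocation was disclosed and T1 WHOQOL after 16 weeks of known allocation. Knowledge of the arm can therefore enter only the post-baseline score, and so goes directly into the between-arm comparison of change. A reader who relies on the blinding sentence would take that comparison as blind-assessed.

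The administered MoCA is the outcome where a blind rater could really help, and the T1 setting in the MBHP arm makes it uncertain that this protection is in place.

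**Working it through.** No figure of the plan is in dispute, so the check sets the sections side by side.

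**1. Who rates each outcome at T1 and T2?** Table 2 has ten rows. The CDR is marked at baseline only, which leaves 10 − 1 = 9 outcome measures at T1 and T2.

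| Measure | Source of the rating | Can a blind rater protect it? |
|---|---|---|
| WHOQOL-BREF, WHOQOL-OLD (primary) | participant | no |
| MAAS, SCS, DASS-21, DUREL | participant | no |
| PSQI | 19 self-report questions, 5 answered by a third party by phone | not the self-report part |
| MoCA | administered test | yes |
| ADL | mode at T1 and T2 not stated | only if interviewer-applied |

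Six measures, including both primary instruments, rest wholly on the participant's rating. One rests on it in part, and at most two could be blind-rated: 6 + 1 + 2 = 9.

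**2. Does the participant know the arm at that time?** Yes. The arm is disclosed at the lecture before the intervention, and T1 and T2 come later.

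**3. Who fills in the forms?** At recruitment the WHOQOL scales were part of an evaluation applied by staff. For later assessments, the reasons given for paper and for SurveyMonkey both turn on what participants can operate, which points to self-completion. Step 1 does not depend on this, because the rating is the participant's in either case.

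**4. Is collection the same in both arms?** No. The mode is tied to the arm. Baseline WHOQOL was taken before anyone had an arm, so an arm-specific mode can apply to WHOQOL only after baseline. Any effect of mode on the answers then enters the same between-arm difference.

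**5. Is the T1 MoCA blind?** The opening of Materials and Methods gives the control arm no maintenance phase. The T1 setting in Assessment and Outcomes therefore describes the MBHP arm only. If the MoCA is given at that meeting, the person giving it would probably recognise a mindfulness group. The article states neither who gives the MoCA at T1 nor where the control arm is assessed, so blinding is in doubt for the MBHP arm and undetermined for the control arm.

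**6. What is not contradicted?** Blind analysis: raw records differ by mode, but a masked dataset could still be prepared. Blind MoCA assessment at T2: that visit is not tied to a class.

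**The case against.** The strongest reply is that the article hides nothing. The sentence that claims blind assessment also says that participants are unblinded and attributes this to the nature of the intervention. Open participants are unavoidable when mindfulness is compared with a computer class, and a single-blind label is customary. That answers any charge of concealment. It does not make the unrestricted word blind true of a self-rated primary outcome. The Discussion does not fill the gap: it raises response styles and social desirability as a source of false correlations among items, not as bias between arms.

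A second reply concerns the MoCA. A maintenance session lasts one hour. With a subgroup of 19 that is 60/19 ≈ 3.2 minutes per person, and less if subgroups are merged, so the stated T1 occasion may be a date and not the room where testing happens. A condensed article may also leave the assessor's identity to a fuller document. This stands, and is why the T1 MoCA is called doubtful and not unblinded.

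A third reply is that the comparator is an active programme from which the authors also expect benefit, so expectation could be similar in both arms or could favour either one. This also stands. No direction or size of bias is claimed, and no section says that tutors collect data.

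**Conclusion.** As written, the claim of blind outcome assessment is wrong for the primary outcome at T1 and T2 and for the other participant-rated scales. Blinding can cover at most the MoCA, the ADL if interviewer-applied, and the analysis. The conclusion rests on the documents' own description of what WHOQOL measures and when participants learn their arm; it needs no outside figure.

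Three stronger readings might be inferred and are not supported:

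- That the trial has no blinding at all. Nothing contradicts blind analysis, or a blind MoCA rater at T2.
- That the T1 MoCA is shown to be unblinded. The setting is documented for the MBHP arm only, and no assessor is named.
- That the bias can be sized, for example as a share of the target difference. The documents give neither a bias nor the effect size behind the 64 per arm, so any percentage would be one assumption divided by another.

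The point changes how the WHOQOL result may be described and how well the MoCA is protected. It does not change the sample size or the planned analysis.

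**What to change.** **Recruitment, Procedures, and Randomization.** Limit the statement to the rater of the MoCA (and of the ADL, if interviewer-applied) and to the analyst. Add that participants are not blind, that all participant-rated scales including the primary WHOQOL scores are unblinded self-report, and that the primary result will be interpreted as such.

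**Assessment and Outcomes.**
- At T1 and T2, in both arms, have the MoCA and ADL given away from the class session by one of the existing research assistants, who holds only the identification number and has no role in either class.
- Have the self-report scales completed without the mindfulness tutors or the control-class leader present.
- Use one collection mode in both arms.

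**Cost.** A short extra slot in the T1 week, rewording in two sections and a less favourable blinding statement. If paper is chosen as the common mode, the two-person data entry would extend to the control arm. Trial Status describes a study still under way at submission, with follow-up expected to finish in February 2021, so the wording and at least the T2 procedures were then open to change. For any T1 visits already held, the report should state the setting, the assessor and the collection mode actually used.

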### Assessment and Outcomes

The first two assessment points (baseline, post-intervention) will occur over a week before the intervention and on the last meeting of the maintenance group, and the follow-up will occur 1 year after the last meeting of the intervention. For the baseline, the sociodemographic questionnaire, WHOQOL-BREF, WHOQOL-OLD, MoCA, and ADL questionnaire occurred during the recruitment; all the other scales will be applied a week before the intervention starts. The measures of the intervention group will be on sheets of paper as most of the participants are not familiar with using electronic devices. The typing of the data will be made by two people to supervise and to guarantee no typing mistake of the collected data. SurveyMonkey software will be used for data collection for control group as the participants will learn how to use it on the cognitive stimulation classes. All the instruments have been validated into Portuguese with reliable psychometric properties and are available in Supplementary Files (48, 49, 60, 61, 63, 65, 68, 70, 71, 73).

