## Materials and Methods

The “MBHP-Elderly Study” is a randomized controlled trial addressing older people with 3 assessment points (baseline, post-intervention, and 1-year follow-up) nested in a cohort study (the EPIDOSO study) of older adults patients assisted in a PC facility of the “Center for Aging Research” [Centro de Estudos do Envelhecimento (CEE)] of the Universidade Federal de São Paulo—UNIFESP.

One hundred fifty-two participants will be recruited from the cohort and then randomized into the following two experimental groups: (I) MBHP intervention group (76 participants) in which the elderly will have a weekly meeting of an hour and 30 min for 8 weeks to perform the MBI (MBHP protocol) accompanied by extra four 1-h meetings through a maintenance group with all participants after the eighth week (each maintenance session took place fortnightly), totaling a 4-month (16-week) intervention; (II) cognitive stimulation control group (76 participants) of elderly who will take computer-based cognitive stimulation classes for 4 months, once-a-week 1.5-h meetings without maintenance phase, totaling 16 weeks. In both groups, the same assessment for data collection will be applied, and they will be applied in the baseline (T0), post-intervention (T1), and 1-year follow-up (T2). Both interventions will last 16 weeks. However, the reason why the MBHP intervention group will take 12 sessions and the cognitive stimulation control group 15 sessions is because one of the aims in the MBHP intervention is to work on the participants' autonomy in their personal mindfulness practice in daily life through home activities exercises, and we wanted to compare its outcomes with the 4-month weekly meetings of control intervention, which require face-to-face sessions. Study design and participant flow through the trial is shown in Figure 1.

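### T1 is set at a maintenance meeting that only the MBHP arm has, and no route is stated to T1 quality-of-life or unwanted-effect data for people who stop attending

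*Protocol article*

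**What the plan says.** Timing (Assessment and Outcomes): the first two assessments "will occur over a week before the intervention and on the last meeting of the maintenance group". For T2, "the follow-up will occur 1 year after the last meeting of the intervention".

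Arms (Materials and Methods): the MBHP arm has eight weekly sessions followed by four fortnightly maintenance sessions. The control arm has weekly classes "without maintenance phase, totaling 16 weeks". The same section says that both groups receive the same assessments at T0, T1 and T2.

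People who stop attending (the feasibility paragraph that follows the MoCA description): "we will make phone calls to them to ask the reasons why they were absent or did not go on attending the meetings".

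Unwanted effects (same paragraph): "At the post-intervention, the feasibility and adherence of MBHP program among the participants will be assessed through a questionnaire created by our research group". That questionnaire covers home practice, "addressing potential unwanted effects as well".

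Analysis (Statistical Analysis): "All analyses will be conducted using intention-to-treat and per-protocol analyses". Sample Size and Power Calculations sizes the trial on change from baseline at each time point and allows for a loss of up to 15%.

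**The concern.** An intention-to-treat comparison is only as good as the effort to measure everyone who was randomized. Here the T1 measurement is attached to a class meeting. Someone who has left the classes is not there on that day, and the only contact described for that person has another purpose. Read literally, whether the primary outcome is observed at T1 depends on adherence, and adherence may well depend on how the person is faring.

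The same applies to harms. Feasibility is a stated aim, to be judged partly on unwanted effects, and the article itself notes that there is no consensus on the unwanted effects of such programs. Yet the one structured enquiry is a post-intervention questionnaire about MBHP. It has no stated counterpart among controls and no stated route to those who left. The focus groups do not close this gap, because they are drawn from people who attended at least 75% of sessions.

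The T1 anchor is also undefined for controls, who have no maintenance group.

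**Working it through.** **Step 1: the plan's own figures.** Inputs from Sample Size and Power Calculations: 64 per group, power 0.80, alpha 0.05, loss 15%. No effect size is stated. For a two-sided two-sample t-test, an assumed d = 0.5 needs 63.77, so 64 per group. Allowing for loss, 64 / 0.85 = 75.3, so 76 per group and 152 in all. Both figures reproduce.

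**Step 2: how many people are affected.** 0.15 × 152 = 22.8, about 23 people; 0.15 × 76 = 11.4, about 11 per arm.

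**Step 3: power.** At 15% loss, 76 × 0.85 = 64.6 per arm remain, with power 0.805 at d = 0.5. At 20% loss it is 0.781 and at 30% it is 0.724. Loss within the allowance does not cost the stated power, so the issue is bias, which the allowance does not address.

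**Step 4: illustrative bias at T1.** Let L be the fraction lost in an arm and k the amount, in SD, by which leavers would have scored worse than stayers. The completer mean exceeds the mean of everyone randomized to that arm by L × k. The bias in the between-arm difference is L₁k₁ − L₂k₂. The documents give no k, and the values below are assumptions.

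| Loss, arm 1 v arm 2 | Gap k | Bias (SD) | As a share of d = 0.5 |
|---|---|---|---|
| 15% v 15% | 0.25 or 0.5, same in both arms | 0 | 0% |
| 20% v 10% | 0.25 in both arms | 0.20 × 0.25 − 0.10 × 0.25 = 0.025 | 5% |
| 20% v 10% | 0.5 in both arms | 0.20 × 0.5 − 0.10 × 0.5 = 0.05 | 10% |
| 15% v 15% | 0.25 in one arm, 0 in the other | 0.15 × 0.25 = 0.0375 | 7.5% |
| 15% v 15% | 0.5 in one arm, 0 in the other | 0.15 × 0.5 = 0.075 | 15% |

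The 20% v 10% rows keep overall loss at 15% (15.2 + 7.6 = 22.8 people), but one arm exceeds the allowance. The bias favours whichever arm has the larger L × k.

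**Step 5: the T1 anchor.** Eight weekly MBHP sessions plus four fortnightly ones end at 16 weeks. For controls the article gives 16 weeks of weekly classes and also 15 sessions, so even a reading of T1 as the last class does not fix the week until those two statements are reconciled.

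**The case against.** The strongest reply is that the article gives the timing of T1 and does not say that leavers are withdrawn or go unassessed. Both arms are to have the same assessments at all three points. Detailed retention procedures and the handling of missing data commonly sit in a full protocol or analysis plan, and neither is shown. This stands as far as it goes. A reader might infer that the primary outcome will be missing for leavers, or that intention-to-treat cannot be done. The text supports neither. Participants can be analysed as randomized with baseline, T2 and a missing-data method.

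T2 also measures the primary outcome and is not tied to a session. That stands, but it does not repair T1. The trial is sized on change at each time point, and repeated-measures MANOVA in its usual form uses only people observed at every time point.

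A reader might also infer that people who left because of an unwanted effect are never heard. That goes too far, since the call about reasons could reveal it. They would still miss the structured items.

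On the control arm, both interventions last 16 weeks, so the intended timing can be guessed. Control data come through SurveyMonkey, which does not itself require attendance, although the article justifies it by what participants learn in class.

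Finally, the bias figures depend on chosen gaps and vanish when loss and gap are equal in both arms. That also stands.

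**Conclusion.** The point holds in a limited form. The article ties T1 to a meeting that exists in one arm only and states no route to T1 WHOQOL or structured unwanted-effect data for people who stop attending. T1 missingness is then likely to follow adherence, and the intention-to-treat comparison at T1 risks becoming a completer comparison.

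The likely distortion is modest. Under the gaps assumed above it runs from 0 to 0.075 SD, up to 15% of the d = 0.5 that 64 per group implies. Both the gaps and d = 0.5 are assumptions. The sample-size arithmetic is sound and is not in question. This is a cheap improvement to data collection and does not show the trial to be invalid.

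**What to change.** - Define T1 as week 16 from class start in both arms.
- At that time seek WHOQOL-BREF, WHOQOL-OLD and the unwanted-effect items from every randomized participant whatever their attendance: at the centre, by post, or by telephone as a fallback. Apply the same rule in both arms and flag the mode of each answer.
- Make this contact at week 16, not when someone stops attending; otherwise the scores belong to the wrong time point.
- Keep it separate from the call about reasons for leaving. A caller who asks why someone left the classes may learn the allocation, and the article promises blind outcome assessment.
- Put the general unwanted-effect items to controls too, so that the MBHP rate has a comparator.
- Seek leavers at T2 on the same terms.

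The cost is one further timed contact with about 23 people at the planned 15% loss, plus a few items for controls. The downside is that some answers arrive in a different mode. Trial Status has recruitment under way since June 2018 and follow-up running to February 2021, so the change helps T2 and whatever T1 collection remained when it is made.
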